#### PA + SB + Sleep Group (Integrated Approach)

The intervention strategies for the integrated approach group will be the same as for the dyadic approach group except that the intervention content will target sleep hygiene in addition to PA and SB (Table 1). For example, the sleep recommendations for young children and strategies to change parents' practices related to their children's sleep hygiene will be provided.

**Table 1 T1:** Strategies and behavior change techniques involved in the PA + SB + sleep group.

**Approach**	**Time**	**Strategies**	**Behavior change technique (code) (53)**	**Contents**
Education materials	Week 1 & 2	Attitude toward the behavior, subjective norm, monitoring, goal setting	Information about health consequences (5.1) Information of others' approval (6.3) Feedback on behavior (2.2) Discrepancy between current behavior and goal (1.6) Goal-setting (behavior) (1.1)	1. WHO 24-h movement guidelines for preschoolers 2. Benefits of having a healthy lifestyle (i.e., high physical activity, low sedentary behavior, low screen time, sufficient sleep) for preschoolers 3. What important others think about the behavior 4. Individual report on children's current level of movement behaviors and the gap with the guidelines5. Steps and strategies of goal-setting (e.g., SMART goals)
	Week 3 & 4	Planning, intention	Action planning (1.4) Non-specific incentive (10.6)	1. Examples of improving physical activity, reduce sedentary behavior, and improve sleep 2. Examples of giving incentives for child when he/she make effort/progress in performing the behavior
	Week 5 & 6	Perceived behavioral control, planning, intention	Problem-solving (1.2) Action planning (1.4) Non-specific incentive (10.6)	1. Strategies to overcome barriers2. Examples of improving physical activity, reduce sedentary behavior, and improve sleep3. Examples of giving incentives for child when he/she make effort/progress in performing the behavior
	Week 7 & 8	Monitoring, perceived behavioral control, planning, habit development	Feedback on behavior (2.2) Problem-solving (1.2) Action planning (1.4) Habit formation (8.3)	1. Individual report on children's current level of movement behaviors and the gap with the guidelines2. Strategies to overcome barriers 3. Examples of improving physical activity, reduce sedentary behavior, and improve sleep 4. Examples of habits
	Week 9 & 10	Planning, habit development	Action planning (1.4) Behavioral substitution (8.2) Habit formation (8.3)	1. Examples of improving physical activity, reduce sedentary behavior, and improve sleep 2. Strategies for developing habits (substitution, repetition)
	Week 11 & 12	Monitoring, habit development	Feedback on behavior (2.2) Behavioral substitution (8.2) Habit formation (8.3)	1. Individual report on the change of children's movement behaviors during the past 10 weeks (based on parent-reported interactive questionnaires) 2. Strategies for developing habits (substitution, repetition)
Workshops	Week 1	Subjective norm, attitude toward the behavior, goal setting	Information of others' approval (6.3) Information about health consequences (5.1) Goal-setting (behavior) (1.1)	1. Introduction of the program 2. WHO 24-h movement guidelines for preschoolers 3. Benefits of having a healthy lifestyle (i.e., high PA, low SB, low screen time, sufficient sleep) for preschoolers 4. Steps and strategies of goal setting
	Week 3	Perceived behavioral control, intention	Problem-solving (1.2) Verbal persuasion about capability (15.1)	1. Solve problems that families have faced using materials 2. Provide strategies to parental perceived barriers 3. Sharing experiences 4. Encouraging families to comply with the intervention
	Week 6	Perceived behavioral control, intention, habit development	Problem-solving (1.2) Verbal persuasion about capability (15.1) Habit formation (8.3)	1. Provide strategies to parental perceived barriers 2. Sharing experiences 3. Encouraging families to comply with the intervention 4. Example of habits 5. Strategies for developing habits
Interactive questionnaires	Week 2, 4, 6, 8, & 10	Goal setting, monitoring	Review behavior goals (1.5) Self-monitoring of behavior (2.3)	1. Movement behaviors over the past two weeks (duration, whether achieve the goal or not) 2. Bi-weekly goals for each movement behavior 3. Reminders of materials use

#### Wait-List Control Group

Parents in the wait-list control group will not receive the intervention. They will be given access to the educational materials after the intervention and follow-up.

### Outcomes

#### Primary Outcomes

##### Activity Sleep Index

Similar to the activity-sleep index created for adults (27), a composite movement behavior score will be created to summarize the multiple dimensions of PA, SB, and sleep among preschoolers. The composite movement behavior score will comprise scores for the following six dimensions representing broad variables that have been examined in relation to the 24-h movement guidelines (28, 29) and in previous studies on sleep among young children (30):

PA: total time on PA of all intensities.PA: total time on MVPA.Screen time.Sleep: bedtime duration (time in bed).Sleep: sleep onset variability (variability in sleep onset times).Sleep: morning wake-time variability (variability in wake times).

Each item will be rescaled from 0 to 10, with a higher score indicating healthier movement behaviors. The formula for rescaling is as follows (27):

$$\begin{array}{l} Rescaled\;score\;=\;\left(\frac{\left(X-X_{\min}\right)}{X_{Range}}\right)\times 10 \end{array}$$

where *X* is the observed value, *X*_min_ is the minimum value observed, and *X*_range_ is the difference between the maximum and minimum values observed (27). A total score ranging from 0 to 60 will be obtained by summing the scores for all items, with higher scores indicating healthier movement behaviors.

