## Introduction

A healthy lifestyle developed in early childhood is associated with numerous health indicators and tracks into later life (1). Physical activity (PA) (2), sedentary behavior (SB) (3), and sleep (4) in isolation are associated with health in the early years. In addition to their individual effects, the integrated effect of all three movement behaviors in a 24-h day has attracted attention. The World Health Organization (WHO) released 24-h movement guidelines for children under 5 years of age in 2019. Specifically, a healthy day for preschoolers aged between 3 and 4 years should include at least 180 min of PA, of which at least 60 min should be moderate-to-vigorous-intensity PA (MVPA); less than 60 min of sedentary screen time; and 10 to 13 h of good-quality sleep (5). Despite the emerging evidence on 24-h movement behaviors and the promotion of integrated guidelines for the early years, low adherence to the 24-h movement guidelines has been reported in numerous countries (6). In Hong Kong, a recent study found a low compliance rate, with only 2.9% of preschoolers meeting all three 24-h movement guidelines (7). Furthermore, the homeschooling induced by the Coronavirus Disease 2019 (COVID-19) pandemic has led to unfavorable behavior changes. Evidence from several countries indicates that since the outbreak of the pandemic, preschoolers have become more sedentary and had more screen time compared with before the pandemic (8–10). As a result, interventions targeting multiple movement behaviors are warranted and should help to determine best practices for behavior change.

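### The printed rescaling formula for the activity sleep index contradicts its stated direction for screen time and the two sleep-variability items, so half of the 60 points run backwards as written

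*Protocol article*

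**What the plan says.** The protocol article (Outcomes, Activity Sleep Index) lists six items: total physical activity, moderate-to-vigorous activity (MVPA), screen time, time in bed, variability of sleep onset, and variability of morning wake time. Of these it says: "Each item will be rescaled from 0 to 10, with a higher score indicating healthier movement behaviors". One formula follows, (X − Xmin)/Xrange × 10. X is the observed value, Xmin the observed minimum, and Xrange "is the difference between the maximum and minimum values observed". The six scores are summed to a total of 0 to 60, again with higher meaning healthier. No mirrored formula appears anywhere in the article.

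The direction for screen time is explicit elsewhere. The Introduction gives the guideline as "less than 60 min of sedentary screen time; and 10 to 13 h of good-quality sleep", and Table 1 counts low screen time as part of a healthy lifestyle.

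The Abstract gives the index as one example of the primary outcomes, and the Discussion calls it one of two indicators of overall behaviour. Statistical Methods also lists total PA, MVPA, sedentary time, screen time and sleep duration as primary outcomes.

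**The concern.** The instruction on direction and the formula cannot both be followed. An analyst who codes the formula as printed gives 10 points to the child with the most screen time and 10 to the child with the most irregular sleep. The usual range check would not expose this, because six items scored 0 to 10 still total 0 to 60 whichever way they point.

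Improvement in half of the items would then be subtracted from the total. The third hypothesis in the Introduction, that adding sleep beats PA + SB alone, is the most exposed. The index has three sleep items, and two of them, including "sleep onset variability (variability in sleep onset times"), would count against the integrated arm when they improve.

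**Working it through.** **Inputs.** The formula, the six items and the 0 to 60 total come from the Activity Sleep Index section. The healthy direction for screen time comes from the Introduction and Table 1. For the two variability items the article does not state a direction; I take less variability as healthier. Longer time in bed is taken as better, as the formula implies.

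**Plan's own figure.** Minimum total 6 × 0 = 0 and maximum 6 × 10 = 60. The stated range reproduces.

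**Direction.** The slope of the score in X is 10/Xrange, which is positive for every item. The score therefore rises with screen time and with both variability measures.

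**Results that need no assumed ranges.** A change of 10% of an item's range moves its score by 1 point.

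| Case | As printed | Three items reversed |
|---|---|---|
| Best on all six items | 10+10+0+10+0+0 = 30 | 60 |
| Worst on all six items | 0+0+10+0+10+10 = 30 | 0 |
| All six improve by 10% of range | +1+1−1+1−1−1 = 0 | +6 |
| Only screen time and the two variability items improve by 10% | −3 | +3 |
| Only the three sleep items improve by 10% | +1−1−1 = −1 | +3 |

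**Effect on the comparison of the two active arms.** Suppose, for illustration, that the PA + SB arm improves total PA, MVPA and screen time by 10% of range, and the integrated arm improves all six items by 10%. As printed, the changes are +1+1−1 = +1 and 0, so the integrated arm looks 1 point worse. With reversal they are +3 and +6, so it is 3 points better.

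**If only the documented direction is used.** Counting screen time alone as reversed, the best child scores 50 and the worst 10 as printed, and a 10% improvement in all six gives +5 − 1 = +4 instead of +6. The contradiction remains but is smaller.

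**Illustration with assumed observed ranges** (total PA 120–420 min, MVPA 20–140 min, screen time 0–240 min, time in bed 8–14 h, each variability SD 5–90 min). Child A has 240 min, 70 min, 30 min, 11 h, 15 min and 15 min. Child B has 160 min, 45 min, 180 min, 9 h, 70 min and 70 min, and is worse on every item.

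- As printed: A = 4.00+4.17+1.25+5.00+1.18+1.18 = 16.8; B = 1.33+2.08+7.50+1.67+7.65+7.65 = 27.9.
- With reversal: A = 4.00+4.17+8.75+5.00+8.82+8.82 = 39.6; B = 1.33+2.08+2.50+1.67+2.35+2.35 = 12.3.

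The order of the two children flips.

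**The case against.** The best defence is intent. The article says twice that higher means healthier, for the items and for the total. The expression is a generic min–max rescale credited to a cited adult index that is not available here. An analyst who puts the direction sentence first would reverse the three items unprompted. A journal article is also condensed, and scoring detail may sit in a fuller document.

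This stands in part: the reversal is probably intended, and the damage arises only if the formula is coded literally. It does not remove the point. The article does not leave the scoring open: it prints a formula, defines each term and applies it to each item. That is a stated rule that conflicts with the sentence before it.

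A reader might infer more, and the documents do not support it:

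- **That this is the lead primary outcome.** It is listed first, but no primary outcome is ranked above the others. Screen time, total PA and MVPA are also analysed separately and are untouched by the error. The two variability items are not in that list.
- **That rewarding longer time in bed is an error of the same kind.** The 10 to 13 h guideline refers to sleep, and time in bed is longer than sleep. Nothing shows how many children would exceed an upper limit. A target-range score is a design preference.
- **That the score scale shifts between visits.** The text does not say whether the observed extremes are taken per visit or pooled, so this follows only if they are recomputed each time.
- **That a standardised effect of 0.73 SD falls to 0.00.** This is 6 × 0.3/√6 = 0.73 against (0.9 − 0.9)/√6 = 0, for independent items with equal scaled SD. Total PA contains MVPA, so independence fails. With an assumed correlation of 0.5 within the two activity items and within the two variability items, the reversed-scoring figure is 1.8/√8 = 0.64. Items are scaled by range, so exact cancellation also needs equal SD-to-range ratios.

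**Conclusion.** The point holds as an internal contradiction in a primary outcome: the formula runs against the stated direction for three of six items. The slope result is algebra and needs no assumed data. The full size, 30 of 60 points, rests on less sleep-timing variability being healthier; for screen time the article itself settles the direction. Exact cancellation requires equal improvement on the rescaled items, which is an illustration and not a forecast. It would be wrong to conclude that the trial's results will be reversed, since that depends on the formula being applied literally. It should nevertheless be corrected before any scoring is done.

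**What to change.** In the Activity Sleep Index section, and wherever the scoring is specified, state (Xmax − X)/Xrange × 10 for screen time, sleep-onset variability and morning wake-time variability. Keep the printed formula for total PA, MVPA and time in bed.

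As a lesser clarification, state that one common set of Xmin and Xmax, pooled over arms, is used at T1 to T4, so that the same behaviour earns the same score at every visit. This does not stop one extreme value from compressing an item. Extremes taken from baseline alone could also let later scores fall outside 0 to 10, so the source of the anchors should be named.

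The cost is a line or two of text and of scoring code. No new data, measurement or change in sample size is involved.

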## Discussion

The aim of the proposed study will be to explore the impact of an integrated movement behaviors (PA + SB + sleep) intervention on promoting overall 24-h movement behaviors (based on activity sleep index and compositional data) and to evaluate how changes in overall 24-h movement behaviors mediate the effect of interventions on health outcomes among preschoolers. At the time this study was initiated, to the best of our knowledge, no studies have examined the effect of an intervention targeting change in all 24-h movement behaviors among preschoolers.

Engaging in a healthy combination of movement behaviors has been related to health among young children (1). In Hong Kong, low compliance with the WHO 24-h movement guidelines among preschoolers has been reported, suggesting the need for interventions aimed at improving all three behaviors (7). Although previous interventions have been demonstrated to be effective in improving individual behaviors among preschoolers (11–13), no study has simultaneously targeted all three 24-h movement behaviors using integrated strategies for the early years. To fill this gap, the proposed intervention will target all three behaviors, and we will examine how these behaviors change as a whole. Two indicators—an activity sleep index and compositional behavior data—will be used to examine preschoolers' overall behaviors. The activity sleep index provides a total score for different dimensions of movement behaviors, with a higher score indicating better overall movement behaviors (27). This indicator may therefore better reflect the overall pattern of 24-h movement behaviors (total PA, MVPA, screen time, and duration and timing of sleep) and can provide insight into how different behaviors change simultaneously. The other primary outcome will be compositional data that reveal the time spent on one behavior relative to other behaviors, which has been increasingly used (31). Previous studies have used compositional data analysis when examining 24-h movement behaviors and health outcomes among preschool-aged children, but most of them applied cross-sectional designs and measured sleep duration subjectively (44–47). Therefore, an intervention study adopting device-based measurement is needed to objectively explore the effect on compositional behavior data in this age group.

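### The activity sleep index prints one increasing rescaling formula for all six items, which contradicts its own rule that higher is healthier for screen time and, on the ordinary reading, for the two sleep-variability items

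*Protocol article*

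**What the plan says.** The protocol article (Outcomes, Primary Outcomes, Activity Sleep Index) builds the index from six items: "The composite movement behavior score will comprise scores for the following six dimensions". These are total physical activity, MVPA, screen time, time in bed, and two timing items: "sleep onset variability (variability in sleep onset times") and "morning wake-time variability (variability in wake times").

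The scoring rule is: "Each item will be rescaled from 0 to 10, with a higher score indicating healthier movement behaviors. The formula for rescaling is as follows". One formula follows, (X − Xmin)/Xrange × 10. X is the observed value, Xmin "is the minimum value observed, and" Xrange "is the difference between the maximum and minimum values observed". The six scores are added to a total of 0 to 60, again read as healthier when higher. The Discussion repeats that reading of the total: "with a higher score indicating better overall movement behaviors (27").

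The article contains no second formula, no reverse-scoring statement and no exception for any item.

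On what counts as healthy, the Introduction cites a guideline of under 60 minutes of sedentary screen time a day. Table 1 lists low screen time as part of the healthy lifestyle taught to parents. No section gives the healthy direction for variability in sleep onset or wake time.

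**The concern.** The printed formula gives 10 to the largest observed value and 0 to the smallest. That matches the stated direction for total physical activity, MVPA and time in bed. For screen time it does the opposite: the child with the most screen time scores 10. If irregular sleep timing is the less healthy state, the same happens with both variability items. The stated meaning of the score and the formula meant to deliver it cannot both hold for these items.

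The index is named among the primary outcomes in the Abstract, and the Discussion makes it one of two indicators of overall movement behavior. If the formula is applied as printed, improvements on some items cancel improvements on others. The contrast between the two intervention arms is the most exposed: those arms differ only in the sleep content, and two of the three sleep items in the index are variability items.

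**Working it through.** **Inputs.** From the Activity Sleep Index section: six items, each scored 0 to 10, formula (X − Xmin)/Xrange × 10. The healthy direction of screen time (lower) comes from the Introduction and Table 1. The healthy direction of the two variability items (lower) is an assumption.

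**The plan's own figure.** Six items at 0 give 6 × 0 = 0, and six at 10 give 6 × 10 = 60. The stated range of 0 to 60 is arithmetically right. What fails is its direction.

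**Extreme profiles.** Take a child at the healthiest observed value on every item, and one at the least healthy.

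- As printed, healthiest: physical activity, MVPA and time in bed at their maxima give 3 × 10 = 30. Screen time and both variabilities at their minima give 3 × 0 = 0. Total 30.
- As printed, least healthy: 3 × 0 + 3 × 10 = 30.
- With (Xmax − X)/Xrange × 10 for the three adverse items: 60 and 0.

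If only the documented contradiction (screen time) is counted, and the printed formula is taken as right for the variability items, 10 of the 60 points are inverted. The two profiles then score 5 × 10 + 0 = 50 and 5 × 0 + 10 = 10.

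**Equal improvement on all six items.** Let each item improve by 10% of its range, which is 1 point per item.

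- As printed: +3 − 3 = 0.
- With reversal: +6.
- If only screen time is inverted: +5 − 1 = +4.

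**Daytime items only.** If total physical activity, MVPA and screen time each improve by 10% of range, the total changes by +1 + 1 − 1 = +1 as printed and by +3 with reversal.

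**Sleep items only.** This is the integrated-versus-dyadic contrast if the two arms do equally well on the three daytime items. Let p_T be the gain in time in bed, and p_on and p_wake the reductions in the two variabilities, each as a share of its range.

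- As printed: change = 10 × (p_T − p_on − p_wake).
- With reversal: change = 10 × (p_T + p_on + p_wake).

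| Time in bed | Each variability item | As printed | With reversal |
|---|---|---|---|
| 10% | 10% | −1.0 | +3.0 |
| 10% | 20% | −3.0 | +5.0 |
| 0% | 10% | −2.0 | +2.0 |
| 20% | 10% | 0.0 | +4.0 |
| 30% | 10% | +1.0 | +5.0 |

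The printed version understates the contrast whenever variability falls. Its sign reverses only if p_T < p_on + p_wake. The percentages are illustrative; the article gives no expected effects on these items.

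**The case against.** The strongest reply is that the intent is not in doubt. The text says for each item, and again for the total, that higher is healthier. An analyst who follows that sentence must reverse the adverse items. The formula is generic min-max scaling taken from a cited source, and a condensed article may leave item-level scoring to a fuller document. What stands is that the article shows an omitted reversal. A reader might infer that the trial will compute the index backwards; the document does not show that. But the article does not leave the scoring open either. It prints a formula, applies it to every item and interprets the total, so the printed rule is wrong as it stands.

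Second, only the direction of screen time is documented. This is correct, and it is why the size is given as up to 30 points.

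Third, a reader might infer that an effective sleep component must lower the index, or that the contrast between the intervention arms necessarily points the wrong way. Neither follows. Time in bed is a sleep item that scores in the stated direction, and the table above includes cases of 0.0 and +1.0. The article's description of the sleep content gives no basis for assuming equal effects on duration and on regularity.

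Fourth, the superiority hypothesis for the integrated arm does not rest on the index alone. Statistical Methods also names total physical activity, MVPA, sedentary time, screen time and sleep duration as primary, and compositional data are a further primary outcome. None of these uses the index formula. A backwards index would also sit visibly at odds with the separately analysed screen time. This limits the damage to the index without repairing it.

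**Conclusion.** The point holds as a contradiction between a printed formula and the stated meaning of a primary outcome. It is certain for screen time (10 of 60 points). It extends to 30 of 60 points if greater variability in sleep onset and wake time is less healthy, which is the ordinary reading but is not stated.

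On that reading, the index scored literally cannot separate the healthiest profile from the least healthy, and equal improvement across all items leaves it unchanged. The effect on the integrated-versus-dyadic comparison is conditional: attenuation whenever variability falls, and reversal only when the two variability reductions together exceed the time-in-bed gain as shares of range, with the daytime items equal between arms.

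It should be corrected because the definition of a primary outcome should not depend on the analyst departing from the printed rule. As the article stands, a later reader could not tell which scoring had been used.

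**What to change.** Before outcome data are analysed by arm, state in the index definition that:

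- screen time, sleep onset variability and wake-time variability are scored as ((Xmax − X)/Xrange) × 10;
- total physical activity, MVPA and time in bed keep the printed formula, ((X − Xmin)/Xrange) × 10;
- the healthy direction is written beside each of the six items, so that the direction of the variability items no longer has to be inferred.

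The cost is one formula and a short statement of directions. No new data are needed, and the 0 to 60 range is unchanged.
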